##### Salivary α-Amylase, Cortisol, and Melatonin levels

Salivary samples will be collected by patients using the passive secretion drooling method. Two samples of saliva from each patient will be collected in 24 hours. At least 1 mL is required for analysis. The putative salivary indicators will be assayed with enzyme-linked immunosorbent assay (ELISA): cortisol (DRG Salivary Cortisol ELISA, DRG Instruments GmbH) and melatonin (DRG Instruments GmbH). Salivary α-amylase (sAA) will be determined with an α-amylase kit (Salimetrics) [93].

##### Cortisol Levels in Hair Samples

Three single 3-cm-long locks of hair will be collected from each patient to measure hair cortisol levels in a 3-month period (assuming an average growth rate of 1 cm per month). After collection, each hair sample will be wrapped in aluminum foil to protect it from light and humidity until analysis. The cortisol level in each sample will be measured using the Cortisol Hair ELISA kit (Alpco Diagnostics) with phosphate-buffered saline (PBS) at pH 8.0.

#### Randomization

All patients who provide written informed consent for participation and meet the eligibility criteria will be randomized and assigned using the online SAS Proc Plan permuted-block randomization with variable block sizes and assignments in sequentially numbered codes provided by the central randomization service on its website [94]. The randomization code will not be released until the patient has been recruited into the trial after baseline measurements have been completed.

An administrative assistant not otherwise involved in the study will provide the next treatment code in the sequence and will record the assignment in a confidential log.

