**Methods:**

We have developed a low-cost therapy protocol for patients with RP with sleep disorders and negative psychological stress. Patients will be randomized to receive a combined intervention with SWL-blocking filters and OM, SWL-blocking filters alone, or OM alone. There will also be a nonintervention arm as a control group. This study will be conducted across 2 retinal units in patients with RP with sleep disorders and high perceived stress and anxiety score reports. Patients will be assessed in the preintervention period, weekly during the 4 weeks of intervention, and then at 6 months postintervention. The primary outcomes are the differences in changes from baseline to postintervention in hormone release (α-amylase, cortisol, and melatonin) and sleep quality, as measured with the visual analog scale. Secondary outcome measures include clinical macular changes, as measured with optical coherence tomography and optical coherence tomography angiography; retinal function, as measured using the visual field and best-corrected visual acuity; sleep data collected from personal wearables; and several patient-reported variables, such as self-recorded sleep diaries, quality of life, perceived stress, and functional status.

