## Methods

### Overview

This parallel-group RCT will be performed at a single institution, which is a tertiary referral hospital with an affiliated research institute (Institute of Applied Ophthalmobiology [IOBA], University of Valladolid). The retinal units in both institutions are highly specialized to manage inherited retinal dystrophies and other related retinal eye diseases. Additionally, the IOBA has a clinical trial unit that could help with the local ethical requirements for running a clinical trial and any oversight or external auditing of data that is needed.

There will be 4 parallel groups of patients. Recruitment will be facilitated by a local foundation for patients with retinitis pigmentosa called the Retina Castilla y León (ReCYL) and will be tightly supervised by an ophthalmologist with specialization in retinal degenerations. Figure 1 provides a summary of the clinical pathways.

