### Patient Selection, Recruitment, Randomization, and Blinding

#### Eligibility

Eligibility will be determined based on the inclusion and exclusion criteria listed in Table 2. Eligible participants will be identified after initial evaluation by a staff ophthalmologist, determined to satisfy 1 of the qualifying procedures, and approached for informed consent by the ophthalmologist and research staff. At this time, patients will watch an introductory video explaining the purpose of the clinical trial. The physician also will lead an in-depth preintervention discussion explaining each approach to stress and sleep disability (SWL and OM vs control) and postintervention expectations. If patients decline to participate in the RCT, they will be presented with the option of enrolling in the control group (no intervention). There will be no restrictions on patient care due to enrollment in the study.

**Table 2 table2:** Inclusion and exclusion criteria at screening.

Inclusion criteria	Exclusion criteria
Age 18-65 years, from ReCYL^a^ Diagnosis of moderate or severe RP^b^ (grading severity scale score>1 point) Visual function enough to tolerate and see through the optic filters during daily activities Written informed consent provided	Underwent any ocular surgery within the previous 6 months Involvement in any other ongoing clinical trial Pregnancy and lactation or under hormonal treatment Allergy or hypersensitivity to melatonin Previous or current therapy with melatonin Autoimmune diseases NSAID^c^ and others anti-inflammatory drug treatment Psychiatric disorders or under any psychotropic medication

^a^ReCYL: Retina Castilla y León.

^b^RP: retinitis pigmentosa.

^c^NSAID: nonsteroidal anti-inflammatory drug.

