### Data Collection and Outcome Measures

#### Baseline Assessments and Frequency of Follow-Up Assessments

A full list of assessments obtained at each time point is summarized in Table 3.

We will obtain baseline assessments during each patient’s screening visit. These measures will include, but will be not limited to, demographics, comorbidities, subjective sleep quality and perceived stress rating, ophthalmic and laboratory outcomes, and patient-reported outcomes specific to the planned intervention.

Initial follow-up assessments will be obtained at 1, 2, 3, and 4 weeks after the start of the intervention. Patients will also be asked to return for postintervention follow-up visits 6 months after the intervention. These visits will be scheduled at the beginning of the study. Patients unable to attend any in-person visit will be asked to at least provide all subjective patient-reported outcomes over the phone or via an electronic survey for that visit in order to facilitate retention and optimal follow-up.

Sleep quality level, laboratory outcomes, ophthalmic clinical outcomes, questionnaire patient-reported outcomes, and potential complications will be gathered during these visits.

**Table 3 table3:** Assessments and follow-up.

Clinical and laboratory event	V_–1_^a^ (–4 weeks)	V_0_ (0 weeks)	V_1_ (1 weeks)	V_2_ (2 weeks)	V_3_ (3 weeks)	V_4_ (4 weeks)	V_F_ (6 months)
Screening	✓^b^	—^c^	—	—	—	—	—
Clinical	—	✓	—	—	—	✓	✓
Physical examination	—	✓	—	—	—	✓	✓
Salivary sample collection	—	✓	✓	✓	✓	✓	—
Hair sample collection	—	✓	—	—	—	✓	—
STAI^d^ questionnaire	—	✓	—	—	—	✓	—
ESS^e^ and PSQI^f^ questionnaires	—	✓	—	—	—	✓	—
Inclusion criteria	✓	—	—	—	—	—	—

^a^V: visit; V_–1_, screening visit, when inclusion and exclusion criteria will be checked; V_0_, visit to assess baseline characteristics; V_1_-V_4_, visits during the intervention period (every week); and V_F_, final visit after 6-month follow-up.

^b^✓: applicable.

^c^Not applicable.

^d^STAI: State-Trait Anxiety Inventory.

^e^ESS: Epworth Sleepiness Scale.

^f^PSQI: Pittsburgh Sleep Quality Index.

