### Limitations

The limitations that may be encountered in the application of this clinical trial are likely to be related to the large phenotypic and genotypic variability found among patients with RP; the difficulties in recruiting patients who meet the eligibility criteria, especially those with enough visual acuity that allows them to use the filters; and the subjective nature of the results of the questionnaires. However, this could be overcome by a good baseline study that allows for proper analysis that considers possible confounding variables. However, a sleep-monitoring device could be used, such as second-generation multisensory sleep trackers, but their price would increase the cost of the study and there is still no validated device for this purpose, so for the time being, they have not been included in the study protocol [122].

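### RP severity is known before randomisation, but no stratum is named and adjustment for it is left to significance-based selection from a covariate list that omits it; this costs precision and credibility, not validity

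*Protocol article*

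**What the plan says.** **Allocation.** Under Randomization, patients are "randomized and assigned using the online SAS Proc Plan permuted-block randomization with variable block sizes". Codes are sequentially numbered, and an assistant hands out the next one in the sequence. No stratum is named there, in Overview or in Study Population.

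**Timing.** Moderate or severe RP (a grading score above 1) is an inclusion criterion in Table 2. The notes to Table 3 describe the "screening visit, when inclusion and exclusion criteria will be checked". Randomization adds: "The randomization code will not be released until the patient has been recruited into the trial after baseline measurements have been completed". The severity score is therefore on file before allocation.

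**Adjustment.** Covariates and Confounders lists preintervention sleep scores, comorbidities, medication, alcohol, tobacco and basic demographics, but neither RP severity nor unit. Statistics names no covariate for the linear mixed model of the hormones. It puts severity and the primary outcomes into a multiple linear regression without saying that treatment is in that model. Treatment effects are then to be adjusted for covariates with significant effects, after variable selection. Limitations cites the "large phenotypic and genotypic variability found among patients with RP" and relies on baseline data and later analysis to deal with it.

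**Units.** The Abstract says: "This study will be conducted across 2 retinal units". Overview says: "This parallel-group RCT will be performed at a single institution", and then refers to the retinal units of both institutions. Laboratory Assessment has samples collected in the same room.

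**The concern.** The article treats severity as relevant to the primary outcomes and knows it in time, yet neither of the usual protections is fixed. Blocking on order of entry balances arm sizes, not severity. In arms of 12 to 15, a visible severity difference somewhere in the baseline table is likely. The fallback is then a rule under which severity enters only if it passes a selection step, and the candidate list does not even name it.

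What is at stake is precision in a small trial, and how far readers trust an effect whose adjustment set was chosen after seeing the data. The unit question matters for the same reason: whether unit is a possible blocking or model factor cannot be settled while the article describes the setting in two ways.

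**Working it through.** **Inputs from the article.** Four equal arms; 12 per arm, raised to 15 for dropout of about 20% (12 / 0.80 = 15). The article gives no figure for imbalance, so there is none to reproduce.

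**Assumptions.** Severe share 20%, 30% or 50%; block sizes 4 and 8; all four arms randomised.

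**1. Simulation, 8,000 trials per setting, no stratification.** Gaps are in percentage points of severe share.

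| Per arm | Severe share | Largest of four arms, gap ≥20 | Largest, gap ≥30 | Given pair, gap ≥20 | Given pair, gap ≥30 |
|---|---|---|---|---|---|
| 12 | 50% | 74% | 47% | 31% | 15% |
| 12 | 30% | 69% | 39% | 28% | 12% |
| 12 | 20% | 56% | 25% | 20% | 7% |
| 15 | 50% | 77% | 35% | 34% | 10% |
| 15 | 30% | 72% | 27% | 29% | 7% |
| 15 | 20% | 61% | 16% | 23% | 4% |

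A repeat at 60 patients gave 62-78% for the largest gap and 23-36% for a given pair at 20 points. Hence the overall ranges of 56-78% and 20-36%.

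**2. Check by hand.** For one pair with exactly 15 per arm and a severe share of 50%, 20 points is 3 patients. With X and Y each Bin(15, 0.5), X − Y + 15 is Bin(30, 0.5), so P(|X − Y| ≥ 3) = 2 × P(Bin(30, 0.5) ≤ 12) = 2 × 0.181 = 0.36. This agrees with the upper end for a given pair.

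**3. Severity as a continuous score.** A given pair differs by more than 0.5 SD in about 22% of trials (12 per arm) or 17% (15 per arm). Some pair among the four does so in about 61% or 52%.

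**4. Blocks within severity grade (severe share 50%).** The mean largest gap falls from 26-29 points to about 4-6. No gap of 20 points occurred in 8,000 trials per setting.

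**5. What a severity term buys.** If severe and moderate patients differ by δ within-grade SDs in the outcome and the severe share is p, omitting severity multiplies the residual variance by 1 + δ²p(1 − p).
- δ = 0.8, p = 0.5: 1 + 0.64 × 0.25 = 1.16; 1/√1.16 = 0.928, a standard error about 7% smaller.
- δ = 0.8, p = 0.2: 1 + 0.64 × 0.16 = 1.102; 1/√1.102 = 0.952, about 5% smaller.
- δ = 0.5, p = 0.5: 1 + 0.25 × 0.25 = 1.0625; 1/√1.0625 = 0.970, about 3% smaller.

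After the cost of estimating the term, the gain at δ = 0.8 is about 4-6%. Stratifying as well adds essentially nothing to precision beyond that. The values of δ are assumptions; the article gives none.

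**The case against.** - **Silence in a condensed article.** The article does not say the list is unstratified, and the full protocol may name strata. This stands, although a single next code in the sequence reads most naturally as one list. The point therefore rests mainly on what the article does fix: selection by significance from a list without severity.
- **Not stratifying is a legitimate choice.** Chance imbalance under proper randomisation does not bias the test, and the standard error already allows for it. This stands in full.
- **Severity is not ignored.** The Statistics section does regress the primary outcomes on graded severity. That is true, but the text does not commit to severity in the model that estimates the treatment effect.
- **The four-arm figure overstates the risk.** A reader might infer that any treatment-control comparison will usually be imbalanced. The given-pair columns do not support that. A reader might also take a 30-point gap with δ = 0.8, giving 0.30 × 0.8 = 0.24 SD or 40% of the article's effect size of 0.6, as the expected distortion. At 15 per arm a given pair reaches that gap in only about 4-10% of trials, and δ = 0.8 is assumed. The primary outcomes are also changes from baseline, so a stable difference in level largely cancels; severity would have to predict the change.
- **Units.** Overview describes a hospital with an affiliated research institute, which may be what both institutions means. Nothing says that sampling takes place at both, and Ancillary Tests assigns OCTA to a single examiner. So noise from two rooms or several examiners is not established. The wording still conflicts and needs settling.

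**Conclusion.** The point holds as one of precision and credibility. No stratification factor is named, severity is available before allocation, and its adjustment is left to significance-based selection from a list that omits it. The imbalance figures rest on the assumed severe share, the assumed block sizes and four randomised arms. The gain from a severity term is modest: about 4-6% in the standard error under a fairly strong assumed severity effect, and less under a weaker one. The documents do not support reading this as a validity failure, as bias in the test, or as proof that a single unstratified list will be used.

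One limit applies throughout. Overview and Eligibility place patients who decline randomisation in the control group, while Study Population and Randomization have all four groups randomised. Neither stratification nor the simulated balance carries over to an arm filled by refusal. That is a separate and weightier defect.

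**What to change.** - **Statistics; Covariates and Confounders.** Name the baseline RP severity score as a fixed covariate in the primary hormone and sleep models, outside any variable selection. Using the score avoids needing a moderate/severe cut-off, which the article does not give. For ESS and PSQI this means a linear model, because the chi-square or Fisher comparison named for these scores cannot carry a covariate. Cost: one model term on data already collected, with no change in sample size.
- **Randomization (optional).** Generate the blocks separately by severity grade and state the cut-off. This mainly improves the look of the baseline table. Cost: one field at randomisation and a few incomplete blocks, so arm totals may differ by one or two patients.
- **Abstract and Overview.** State the number of units. If patients are sampled at two, add unit as a fixed term and align the same-room statement in Laboratory Assessment.
- **Control arm.** Resolve separately how it is formed; the steps above do not balance it.

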#### Blinding

In our double-blinded trial, the principal investigator and statistician will be blinded to treatment allocation. Staff responsible for recruitment and grading severity will not be allowed to receive information about the group allocation. Raters will not be present during the lab analysis. Randomization will be conducted by the central randomization service to keep the principal investigator and statistician blind to the data management and study condition.

In the event of a SUSAR (suspected unexpected serious adverse reaction), if requested by the Data Safety Monitoring Committee (DSMC), or if a medical emergency occurs where knowledge of the blinded treatment is necessary, unblinding will be performed independently of the group allocation. The reporting of all SUSARs needs to be expedited.

### Intervention

All patients will be provided with a leaflet with clear instructions at the baseline visit, and they will be asked to follow the guidelines throughout the 4-week follow-up period.

#### Optical Filters for Blocking SWL

Patients will be provided with SWL-restricting goggles to wear during the daytime, in indoor bright-light conditions, and when using LED electronic devices in order to prevent the suppression of melatonin for at least 30 days. Optical filters will allow selective exclusion of less than 480-nm-wide wavelengths, while maintaining relatively good contrast sensitivity and a visual light transmittance of 70%-75% [95].

#### Oral Melatonin (6 mg)

Patients will be asked to intake a 6 mg melatonin dose orally once a day for 30 days in the evening (22:00 P.M. with a margin of 30 minutes before and after) to activate its sleep-promoting effects approximately 2 hours after intake, avoiding fatigue and sleepiness during the daytime [96-99].

Although the chosen dose is safe to obtain the desired effect, patients will be prompted to report any possible side effects, if present, during the intervention period [79,81,82,100]. If they experience unbearable side effects, they will have to discontinue the OM intervention. If they wish, they can participate in the SWL-blocking intervention and will be evaluated over the 4-week follow-up period.

#### SWL Blocking + Oral Melatonin (6 mg)

Participants in this combination arm will receive both interventions—filter goggles and OM—at the same time under the same conditions as the SWL and OM groups and for the same 30-day period.

#### No Intervention

The purpose of this arm is to serve as the procedural control, so patients in this group will be asked to fill their sleep diaries at home only for the first 2-week period after trial commencement. They will be chosen as comparator to avoid performance bias and other biases related to loss of binding in the trial.

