### Choice of Comparators

To date, therapeutic approaches for RP are restricted to slowing down the degenerative process; treating ocular complications, such as cataracts and macular edema; and helping patients cope with the social and psychological impacts of blindness. In addition, the evidence from RCTs on the visual protective effects of vitamins and nutritional supplementations in patients with RP is limited and in some cases contradictory. Moreover, as mentioned before, few studies on the effects of blocking SWL on visual discrimination capacity in patients with RP have been reported. In addition, in clinical practice, there is insufficient experience to recommend the use of optical absorbing filters, since their potential effects on regulating the human internal circadian (24-hour) clock in patients with RP are yet unknown.

For this reason, the intervention groups will consist of SWL blocking alone (SWL group), OM therapy alone (OM group), and SWL blocking plus OM therapy (SWL+OM group) in order to determine whether there is any summative effect. No intervention has been chosen for comparison to avoid performance bias and other biases related to loss of blinding in the trial. Therefore, as several treatments have been proposed to slow down the degenerative process and the current evidence from their results is still limited, no intervention as the control group is justified for this study.

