A draft intervention protocol will be developed for each group, covering preintervention, intervention, postintervention, and discharge settings based on the literature. A steering committee comprising ophthalmologists, opticians, nurses, psychologists, and the research team will be created to develop these protocols. Additionally, 2 ophthalmology residents will be included. Finally, 1 patient with RP, who is the current president of the Federation of Inherited Retinal Dystrophies’ Associations, will be included in the steering committee. The steering committee members are experts in their respective fields and have used the existing literature (summarized in the *Background and Rationale* section) to inform the inclusion of the different interventions in the protocols. The draft intervention protocols are presented in Table 1. Although the choice of each intervention in these protocols will be informed by the literature [7,28,30,36,51,57,67,75-82] and expert consensus of the steering committee, the study will assess the efficacy of combined interventions in sleep disorders and stress control in a large group of patients with RP. Before the intervention period, all patients will be asked to complete sleep diaries for 2 weeks. In addition, patients in the intervention groups (SWL, OM, SWL+OM) must complete them during the intervention period (30 days). Patients from the SWL and SWL+OM groups will wear SWL-restricting goggles in bright-light conditions and when using light-emitting diode (LED) electronic devices for the 30 days of intervention. Patients from the OM and SWL+OM groups will take 3 pills of Circadin 2 mg (OM) every evening at 10:00 P.M. with a margin of 30 minutes before and after.

A preintervention time of 1.5 years will be necessary for recruitment, informed consent, eligibility screening, and baseline data collection. Next, patients will be randomized to 4 groups in a 1:1 ratio. The treatment groups will include SWL with or without the use of OM. The control group will include patients who are eligible for the study but not willing to be randomized to an intervention sleep and stress management pathway. When the intervention phase (4 weeks) is over, all patients will be followed up for 6 months via standard monitoring. Figure 2 provides a summary of the RCT timeline.

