**Figure 1 figure1:**
[figure not shown]
Flow diagram illustrating the study protocol. At the allocation to interventions, the number of patients who receive the intervention will be registered, as well as those who do not receive it (together with the reason it was not applied) and those who get lost in the follow-up or discontinue the intervention. In addition, unbearable side effects and SUSARs would be appropriately notified and registered. e: patients excluded; r: randomized patients; RP: retinitis pigmentosa; SUSAR: suspected unexpected serious adverse reaction; SWL: short-wavelength light; VA: visual acuity.

**Table 1 table1:** Protocols of the intervention.

Group	Preintervention period (2 weeks)	Intervention period (30 days)
SWL^a^: optical SWL filters	Sleep diary	Sleep diary, goggles
OM^b^	Sleep diary	Sleep diary, OM
SWL+OM: optical SWL filters and OM	Sleep diary	Sleep diary, goggles, OM
Control: no intervention	Sleep diary	None

^a^SWL: short-wavelength light.

^b^OM: oral melatonin.

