##### Sleep Diary

During the 2-week period before trial commencement and the 4-week period of the intervention, patients will fill a daily self-recorded sleep diary at home. The sleep diary will record parameters such as bedtime, wake time, sleep onset, and sleep offset time.

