### Data Management, Analysis, and Additional Information

#### Data Management

In the clinical trial, data handling will be managed by a third-party agency. The investigators, patients, and clinical staff rating or applying therapies will not have access to information until the data analysis is completed by predetermined statisticians. They will also not be aware of the allocation of patients in the trial. Data entry into the virtual system will also be managed by the third-party agency.

Patients’ information will be encrypted in a virtual database, secured, and password-protected. Only the data monitoring committee (DCM) will have access during the trial. Data coding will begin at randomization; SAS will generate an alphanumeric code for each block. An ID number will be assigned to each patient. If a major adverse effect occurs, it will be identified by the ID number.

The software will record any changes made by any person involved in the functioning of the program. The user ID will identify people who make any changes to the system, and this information will be used for the purpose of auditing the trial. During a regulatory audit, the auditors can verify any changes that occur in the system and data. All data will be regularly backed up to a password-secured database.

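### The control arm's sleep diary is specified three ways, mostly leaving no control data during treatment, and the double-blind label does not fit patients who can see what they receive

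*Protocol article*

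**What the plan says.** **Diary.** The protocol article fixes the control arm's diary in four places.

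- Overview: "Before the intervention period, all patients will be asked to complete sleep diaries for 2 weeks". During treatment, "patients in the intervention groups (SWL, OM, SWL+OM) must complete them during the intervention period (30 days"; controls are not in that list.
- Table 1: the row "Control: no intervention" shows a sleep diary before the intervention and nothing in the 30-day period.
- No Intervention: "patients in this group will be asked to fill their sleep diaries at home only for the first 2-week period after trial commencement".
- Sleep Diary section: "During the 2-week period before trial commencement and the 4-week period of the intervention, patients will fill a daily self-recorded sleep diary at home", with no exception for controls.

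The Secondary Outcome Measures section lists the diary as a patient-reported outcome. The Primary Outcome Measures section measures sleep quality by ESS and PSQI. Table 3 schedules both, and STAI, at V0 and V4 without distinguishing arms.

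**Blinding.** The trial is called double-blind in Need for a Trial and in the Discussion's Conclusion. The Blinding section says: "In our double-blinded trial, the principal investigator and statistician will be blinded to treatment allocation". It adds that recruitment and severity-grading staff will not be told the allocation. Data Management goes further. Having named investigators, patients, and clinical staff who rate or apply the therapies, it says: "They will also not be aware of the allocation of patients in the trial". Choice of Comparators justifies the untreated arm thus: "No intervention has been chosen for comparison to avoid performance bias and other biases related to loss of blinding in the trial". The No Intervention section repeats that rationale.

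**The concern.** An outcome can be compared with control only if controls supply it over the same period. If they stop the diary when treatment starts, the diary can describe change in the active arms but cannot separate a treatment effect from time, season or regression to the mean.

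The asymmetry also reaches the questionnaires. Keeping a daily sleep record for 30 days is itself a behavioural exposure, and only the active arms would have it when they complete ESS and PSQI at V4.

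The blinding statements matter for the same outcomes. Someone given goggles, tablets, both or nothing knows which. An untreated control whose members know they are untreated is a source of performance and expectation bias in self-reports, so the stated rationale runs the wrong way. A reader who takes the label at face value would credit the self-reported results with a protection that the design does not give.

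**Working it through.** **1. Diary coverage, set side by side**

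| Source | Controls, before intervention | Controls, during intervention | Active arms, during intervention |
|---|---|---|---|
| Overview | 2 weeks | not required | 30 days |
| Table 1 | diary | none | diary, 30 days |
| No Intervention | not mentioned | at most 14 days | not addressed |
| Sleep Diary | 2 weeks | 4 weeks, if controls are included | 4 weeks |

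The No Intervention entry depends on what trial commencement means. The Sleep Diary section uses the term for the end of the pre-intervention fortnight. Read the same way, controls would keep the diary for the first 14 of 30 days. If it means entry into the study, the sentence could agree with the Overview and Table 1. The article does not say which.

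- Under the Overview and Table 1, control diary days during treatment are 0 against 30, so 0 of 3 active-versus-control comparisons are possible in that period.
- Under the 14-day reading, a partial concurrent comparison exists, but a change from baseline to the end of the intervention cannot be formed for controls.
- Only the Sleep Diary section, read as covering all arms, permits the full comparison.

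**2. Which outcomes are affected**

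- Diary (secondary): control data absent or incomplete during treatment.
- ESS, PSQI (primary) and STAI: scheduled in every arm at V0 and V4. Data are present, but the reports are unblinded and follow unequal self-monitoring.
- Salivary and hair assays (primary): less exposed to expectation.

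**3. Who can be blinded**

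The arms are goggles, melatonin tablets, both, or nothing. No placebo tablet or sham lens is described, and an arm defined as no intervention has neither. Patients therefore cannot be unaware of what they receive, and staff who hand over the intervention cannot be either. The principal investigator, the statistician and the severity-grading staff named in the Blinding section can be kept unaware.

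**4. Illustration of size for the questionnaires**

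The method was first checked on the plan's own figure. For a two-sided two-sample t test at 5% with n = 12 per group and d = 1.2, the noncentrality is d√(n/2) = 1.2 × √6 = 2.94 on 22 degrees of freedom. Power is 80.2%, against the stated 80.02%. Sidedness is not stated; two-sided is assumed.

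Now suppose that the treatment does nothing but unblinded reporting shifts the active-arm mean by δ SD. The documents give no δ; 0.2 to 0.5 is an assumption.

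| δ | n = 12: noncentrality | n = 12: P(significant) | n = 15: P(significant) |
|---|---|---|---|
| 0.2 | 0.2 × √6 = 0.49 | 7.6% | 8.3% |
| 0.5 | 0.5 × √6 = 1.22 | 21.6% | 26.2% |

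The planned 15 per group with the expected 5% to 10% dropout leaves 13.5 to 14.25, so the figures would fall between these columns. These are per contrast, against a nominal 5%. The Statistics section plans chi-square or Fisher tests for these scores, so the t test only gives a sense of scale.

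**The case against.** The best defence is that the damage is confined. The diary is secondary, and its comparisons among the three active arms, including combination against single therapy, are untouched. Weekly calls and visits are not restricted to treated arms, so unequal staff contact is not shown. The objective biomarkers are co-primary. All of this stands and sets the scope of the point.

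A reader might infer four stronger things that the article does not support.

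- *That no self-reported sleep measure is available like-for-like from controls.* Table 3 schedules ESS and PSQI equally in all arms.
- *That the No Intervention sentence itself stops the controls' diary before treatment.* It says after trial commencement; the earlier stop comes from the Overview and Table 1.
- *That every double-blind statement claims patients are blinded.* Only Data Management mentions patients. Need for a Trial and the Conclusion use the label alone, and the Blinding section names other roles.
- *That the 8% to 22% is an estimate of bias in this trial.* It follows from an assumed shift.

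The defence does not remove the contradiction between the diary passages or the statement that patients will not know their allocation. Nor can these be left to a fuller document: the article fixes both, and fixes them badly.

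**Conclusion.** The point holds on both parts, and should be corrected before the trial starts.

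On the diary, the sections conflict. Under the two most explicit, the Overview and Table 1, a secondary outcome has no control data during treatment (0 of 3 comparisons) and daily self-monitoring is confined to active arms.

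On blinding, the double-blind label and the Data Management statement do not fit a design with visibly different arms and no placebo or sham described, and the performance-bias rationale for the untreated control is reversed. The consequence falls on ESS, PSQI, STAI and the diary, and much less on the salivary and hair assays. Its size cannot be derived from the documents.

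A separate matter would remain after this correction. The Overview and Eligibility sections allow patients who decline randomization into the control arm, so matching diaries and accurate labels would not by themselves make active-versus-control contrasts fully comparable.

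**What to change.** - **Diary.** Reconcile the Overview, Table 1, Sleep Diary and No Intervention sections so that all four arms keep the same daily diary for the 2 weeks before and the full 30-day intervention period. State the period as 30 days throughout, since the Sleep Diary section says 4 weeks.
- **Label.** In Need for a Trial, Blinding and the Conclusion, replace double-blind with wording such as: open-label to patients, with the principal investigator, statistician and severity-grading staff blinded. Claim no blinded role that the Blinding section does not name. Correct Data Management so that it no longer says patients and the staff applying therapies are unaware of allocation.
- **Rationale.** Delete from Choice of Comparators and No Intervention the claim that an untreated control avoids performance bias.
- **Interpretation.** State that ESS, PSQI, STAI and diary results are unblinded self-reports, and that the salivary and hair assays are less exposed to expectation.

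The cost is 30 more diary days for 12 to 15 controls (12 × 30 = 360 to 15 × 30 = 450 entries), a small burden, plus wording. The description of blinding becomes less favourable but accurate. The article reports that the trial has not begun, so nothing already collected is affected.
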